### Participant timeline {13}

Figure 1 depicts the patient recruitment, intervention, and evaluation schedule during this study.

### Sample size {14}

Considering the benefits of complex physical therapy when there is a percentage reduction in excess limb volume of 22% to 73% [21], and, for the use of compressive therapy, an estimated response of 33.5% reduction in excess limb volume [22], we stipulated a 35% variation in treatment response between the groups, with an estimated treatment response of 45% in the control group (standard care) and 80% in the intervention group. The sample size was calculated considering a confidence level of 95% with a study power of 80% and a 1:1:1:1 ratio between the intervention groups. Thus, a total population of 120 patients (30 in each group) will be required. To cover possible losses to follow-up and treatment interruption, a total of 20% will be added to the number of participants Therefore, the total sample to be included in this study will be of 144 women (36 in each group).

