### Trial design {8}

The trial design is as follows: single-blind, superiority, randomized controlled clinical trial, with a 1:1 allocation ratio for each group. Phase 1 participants cannot be part of phase 2 study and vice versa.

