## Outcomes {12}

### Primary outcome

#### Lymphedema arm volume

This will be evaluated by determining upper limb perimetry, with reference to the cubital fold, from which points will be measured at 7 cm, 14 cm, and 21 cm below and 7 cm and 14 cm above. The measurements referring to each point will be applied in the trunk cone formula *V* = *h* * (*C*^2^ + *Cc* + *c*^2^)/(π* 12), where *V* is the limb segment volume, *C* and *c* are the circumferences at each end, and *h* is the distance between circles (*C*). This calculation will represent the estimated limb volume [13]. The limb volume percentage reduction will be calculated as (*VI*-*VF*/*VI*)*100, where *VI* comprises the initial volume and *VF* the final volume. The treatment response will be considered effective in phase 1 when an affected upper limb volume reduction of over 10% of the initial volume takes place, while phase 2 therapy success will be linked to volume maintenance or a greater variation of up to 10% of the initial volume of the upper limb presenting lymphedema.

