## Statistical methods

### Statistical methods for primary and secondary outcomes {20a}

A descriptive analysis of the sociodemographic and clinical characteristics of the study population will be carried out through the distribution of absolute and relative frequencies for categorical variables and central tendency and dispersion measures for continuous variables. The thermographic analysis will be obtained by the average difference in temperatures of one limb in relation to the other and a cut-off point will be established. Data normality will be calculated using the Kolmogorov–Smirnov test. Group comparisons will be done by using Student’s *t* test or Wilcoxon test for continuous variables and chi-square test for categorical variables. The effect size of the mean outcomes will be calculated using Glass’s delta (considering 0.2 as small, 0.5 as medium, and 0.8 as large effects) [23]. Associations between the variables of interest and the outcome will be performed using univariate linear regression. Variables presenting *p* ≤ 0.20 will be included in the multiple linear regression model employing the stepwise forward method, and those with *p* < 0.05 or with clinical relevance will be maintained in the adjusted model. A significance level of 5% will be accepted, at a confidence interval of 95%. Statistical tests will be performed using the SPSS version 23.0 software.

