### Methods in analysis to handle protocol non-adherence and any statistical methods to handle missing data {20c}

Outcome assessments will be performed by intention to treat and protocol adherence will be verified.

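### The 20% allowance replaces women who interrupt treatment, and some of them are withdrawn, although the declared analysis is by intention to treat

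*Protocol article*

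**What the plan says.** All references are to the protocol article.

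- **Sample size {14}.** The calculation assumes a treatment response "with an estimated treatment response of 45% in the control group (standard care) and 80% in the intervention group", 95% confidence and 80% power, and concludes that "a total population of 120 patients (30 in each group) will be required". It continues: "To cover possible losses to follow-up and treatment interruption, a total of 20% will be added to the number of participants". The result is 36 per group, 144 in all.
- **Section {20c}**, on non-adherence and missing data: "Outcome assessments will be performed by intention to treat and protocol adherence will be verified".
- **Section {18a}** applies the assessments to every included participant, before and after the first 30 days and at 6 and 12 months.
- **Section {11b}** lists reasons for suspending treatment early. They include allergic reaction, poor adaptation to the material, infection of the limb, and a limb volume more than 10% above its starting value.
- **Section {21a}** says that a participant with unwanted effects of treatment leaves the study and goes to the institutional routine.
- **Outcomes {12}**, primary outcome: "The treatment response will be considered effective in phase 1 when an affected upper limb volume reduction of over 10% of the initial volume takes" (clause cut here). In phase 2, success is a volume that is maintained or varies by no more than 10%.
- **Sections {16b}, {17a} and {17b}**: participants and research physiotherapists know the allocation; only the statistician is blinded.

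**The concern.** Recruiting extra women to make up for those who will have no outcome is ordinary practice. The difficulty is that the allowance also names treatment interruption. Under intention to treat, a woman who stops her garment, bandage or mesh keeps her place in her allocated group, so there is nothing to replace. If 45% and 80% were intention-to-treat rates, the effect of interruptions would already be inside them.

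Section {21a} makes this more than loose wording. If women with unwanted effects leave the study, their later volumes may never be taken, whatever {18a} and {20c} intend. These women are not a random sample. Stopping for a volume rise above 10% is stopping for a failure on the primary outcome, and {22} lists volume worsening of 10% among the adverse events. Each phase compares two different forms of compression with allocation known, so equal interruption in the two arms cannot be taken for granted. What is at stake is a completer comparison reported as intention to treat, with a responder difference shifted by who was removed, and a power figure that belongs to another analysis set.

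**Working it through.** **Inputs.** Rates 0.45 and 0.80, 30 and then 36 per group, and 80% power come from {14}; 1:1 allocation from {8}; the chi-square test for categorical variables and the 5% level from {20a}. Sidedness is not stated, so two-sided 5% is assumed. Each phase is a separate comparison of two groups.

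**1. The plan's own figure.** With the pooled two-proportion formula without continuity correction,

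n = [1.960·√(2p̄(1−p̄)) + 0.842·√(p₁(1−p₁)+p₂(1−p₂))]² / (p₂−p₁)²

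and p̄ = 0.625: n = (1.960·√0.46875 + 0.842·√0.4075)² / 0.35² = (1.342 + 0.537)² / 0.1225 ≈ 28.8, so 29 per group. The stated 30 is reproduced to within one.

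**2. Power of the stated set.** Power = Φ{[(p₂−p₁)·√n − 1.960·√(2p̄(1−p̄))] / √(p₁(1−p₁)+p₂(1−p₂))}. For n = 30: (1.917 − 1.342)/0.638 = 0.901, giving 81.6% (exact enumeration of the chi-square test 81.6%).

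**3. The allowance.** 30 × 1.20 = 36. Six of 36 (24 of 144) is 16.7%, or 1 in 6, and removing them returns the 30 in step 2. The stated power therefore fits the set left after losses and interruptions.

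**4. All 36 per group, with 1 in 6 affected in each arm.**

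| How the affected women enter | Rates | Power |
|---|---|---|
| All scored as non-responders | 0.45×5/6 = 37.5%; 0.80×5/6 = 66.7% | 70.6% (exact 69.5%) |
| Affected experimental women respond at the control rate | 45%; 74.2% | 72.2% |
| All scored as responders | 54.2%; 83.3% | 77.3% |
| Half measured at the planned rates, half non-responders | 41.25%; 73.3% | 79.9% (exact 79.4%) |
| Missing at random, handled as such | 45%; 80% on about 30 | near 81.6% |
| All measured, rates unchanged | 45%; 80% on 36 | 88.3% |

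First row worked: (0.2917×6 − 1.385)/0.676 = 0.541, and Φ(0.541) = 70.6%. Under that scoring, 80% power would need 45 per group.

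**5. Sensitivity to the loss itself.** With non-responder scoring and equal loss, power is 83.4% at 5% loss, 78.1% at 10% and 66.8% at 20%. With unequal loss it is 42.2% (10% control, 23.3% experimental) or 90.8% (the reverse). These two are illustrations; the article gives no arm-specific loss.

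**6. The passages side by side.** {18a} and {20c} keep every included woman measured and analysed. {14} replaces those who interrupt, and {21a} takes some of them out of the study. {11b} suspends treatment without saying whether measurement goes on. A reader cannot satisfy all five.

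**The case against.** The strongest reply is that {14} and {20c} need not conflict. Adding recruits for possible losses is routine in trials analysed by intention to treat, and {14} never says that those women are dropped or that 45% and 80% are completer rates. This stands for losses to follow-up. It does not dispose of treatment interruption, which intention to treat gives no reason to replace, nor of the withdrawal in {21a}.

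A reader might go further and infer three things that the article does not support.

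- **That the trial really has about 70% power.** That figure requires every affected woman to be a non-responder and loss to be equal in both arms. No section says so, and other equal-loss scorings at 1 in 6 give 72% to 88%. The article calls the losses possible, so 1 in 6 is an allowance and not a forecast. The non-responder penalty also does not carry over to the t test, Wilcoxon or regression analyses of volume in {20a}.
- **That the absence of a missing-data rule is itself an error.** The rule may stand in a full protocol or analysis plan that is not shown.
- **That a woman who interrupts but is measured has no score.** Outcomes {12} defines response from initial and final volume with no condition on completing treatment, so she is scored.

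Nor does the article say that the devices differ in tolerability; {21a} presumes no serious adverse effects in either arm. Unequal interruption is a possibility to guard against, not a documented fact. Finally, 115 of 144 women had been included by May 2023, so a restated power changes no recruitment decision. Continued measurement can still matter for women in follow-up.

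**Conclusion.** The point holds as an inconsistency between the sizing and withdrawal provisions on one side and the declared analysis and assessment plan on the other. Followed literally, {14} and {21a} can turn the intention-to-treat responder comparison into a completer comparison, and some of those removed may be outcome failures. The direction and size of the resulting bias cannot be given from the article.

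The sample size of 30 is not wrong for its inputs. What is unsettled is power for all 36 per group: about 70% to 88% with 1 in 6 affected equally in each arm, depending on scoring, under a two-sided 5% test without continuity correction. Outside those assumptions the range is wider. The plan should be amended on this point, but the article does not show that the trial is underpowered.

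**What to change.** 1. Reconcile {11b}, {14}, {18a}, {20c} and {21a}, so that women who stop the allocated compression are still measured at the scheduled visits, unless they withdraw consent, and are analysed in their allocated group. This concerns measurement only and leaves open when treatment should stop.
2. In {14}, limit the 20% allowance to women with no outcome measurement.
3. State whether 45% and 80% already include interruptions. If they do not, restate power for the intention-to-treat responder analysis as a range with its assumptions.
4. Report a sensitivity analysis that counts women with no final volume as non-responders, alongside a missing-at-random analysis. Which of the two should be the main analysis is open to debate, and the article does not settle it.

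The cost is rewording in a few sections and two analyses of data already planned. The stated power may look less favourable. No patients or scheduled visits are added.

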### Recruitment {15}

Volunteer recruitment will take place at the health institution itself, through post-operative breast cancer follow-up consultations conducted in the physiotherapy sector. The researchers will indicate patients scheduled for consultation who meet the eligibility criteria to participate in the research to the physiotherapy team. If accepted, the patient will be forwarded to the research sector to sign the free and informed consent form and be allocated in a treatment group.

## Assignment of interventions: allocation

### Sequence generation {16a}

The choice between the intervention groups is made from the sequential opening of sealed opaque envelopes, and inside each envelope, there was a card numbered from 01 to 36 for group A or B in phase 1 and for group C or D in phase 2. For each participant who agreed to participate in the study, one of the envelopes was open, depending on the intended lymphedema treatment phase, being randomized between an experimental or control group.

### Concealment mechanism {16b}

Sequentially numbered, opaque, sealed envelopes containing the code that determines participant allocation in the experimental or standard group will be made available according to the treatment phase (phase 1 or phase 2), allocated at a 1:1 ratio in each group. Due to the study characteristics, the allocation will not be blinded and will be revealed to both the participant and the researcher after randomization.

### Implementation {16c}

After recruiting by sector physiotherapists, the participants will sign the free and informed consent form alongside the study researchers, and volunteer randomization in each study arm will be carried out. The study group will be revealed to both the patient and the researcher at the same time.

## Assignment of interventions: blinding

### Who will be blinded {17a}

This comprises a simple blind study in which only the statistical researcher responsible for analyzing the collected data will be blinded.

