### Intervention description {11a}

The evaluations, interventions, and data collection steps will be carried out by three professional physiotherapists with at least 2 years of experience in compression therapy, all trained and qualified for this purpose. All participants will be guided on the research procedures and will receive a booklet with guidance on performing daily home upper limb exercises, skin care, and daily living activities according to the applied institutional routine [12], which does not include manual lymphatic drainage. Compression therapy will be indicated according to the treatment phase (1 or 2) and intervention group (experimental or control). Participants will be randomly allocated to the following treatment groups (Fig. 1).

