### Procedure for unblinding if needed {17b}

Due to the study characteristics, both the study participants and the research physiotherapist will be aware of the allocation groups. Consequently, no non-blinding procedure is planned.

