## Oversight and monitoring

### Composition of the coordinating center and trial steering committee {5d}

This is a study developed in a single location and with few researchers involved. Therefore, no judging committee is included. However, team support is available, as follows: the principal investigator assumes the supervision of the judging committee and technical responsibility for the physiotherapeutic conducts applied to the study participants and is also responsible in case of adverse effects; the study project coordinator carries out test registrations, coordinates technical visits, guarantees the reports, and assists in data organization and protection; physiotherapist 1 performs reassessments and organizes and protects data quality; physiotherapist 2 identifies potential recruits, signals the sector’s physiotherapy team, receives patients, informs the protocol, advises on the informed consent form, performs evaluations, and ensures participant follow-up according to the applied protocol.

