### Limitations

Due to the characteristics of this type of study, this clinical trial is single blinded, as there is no possibility of blinding the participants or therapists.

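### Only the statistician is blinded, while physiotherapists who know the allocation measure the primary outcome, and the protocol does not say why the outcome assessor cannot be blinded

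*Protocol article*

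**What the plan says.** All references are to the protocol article.

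- **Blinding.** Under Who will be blinded {17a}, "only the statistical researcher responsible for analyzing the collected data will be blinded". Under Procedure for unblinding {17b}, "both the study participants and the research physiotherapist will be aware of the allocation groups". Under Implementation {16c}, "The study group will be revealed to both the patient and the researcher at the same time".
- **Primary outcome.** Of arm volume it says: "This will be evaluated by determining upper limb perimetry, with reference to the cubital fold". Six circumferences enter a truncated-cone formula. Phase 1 response is counted "when an affected upper limb volume reduction of over 10% of the initial volume takes place". Phase 2 success is also judged against a 10% limit.
- **Who measures.** Intervention description {11a} has evaluation, treatment and data collection "carried out by three professional physiotherapists". Plans for assessment {18a} leaves all data collection to physiotherapists. The role list under {5d} adds that "physiotherapist 1 performs reassessments and organizes and protects data quality", while physiotherapist 2 recruits, advises on consent, evaluates and follows up.
- **Data handling.** Under Data management {19}, two physiotherapists collect the data and enter them in the spreadsheet. A third team member checks the entries against paper.
- **Reason given.** Under Limitations, "there is no possibility of blinding the participants or therapists". Assessors are not mentioned.

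**The concern.** Circumference readings depend on how the examiner places and tensions the tape. If the examiner knows the arm, expectation can enter the reading, and nothing done later by a blinded analyst can take it out. Here the readings decide the primary outcome, which is cut at 10% of initial volume, so a modest shift can move a woman across the line. The participants and the treating staff cannot be blinded. The person holding the tape is a different case, because the limb can be presented bare, and the protocol gives no reason for leaving that person unblinded.

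**Working it through.** **1. Sections side by side.** {17a} blinds one person, who takes no measurements. {16c} and {17b} tell the researcher and the research physiotherapist the group. {11a} and {18a} give measurement to the physiotherapists. No section describes a blinded assessor or another safeguard for the reading. Limitations covers two of the three parties concerned (participants and therapists) and omits the third.

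**2. Sensitivity of volume to the reading.** The protocol gives no measurement error and no circumferences, so the arms below are assumptions. The formula is the protocol's own, summed over five 7 cm segments: V = 7/(12π) × Σ(C² + Cc + c²), where 7/(12π) = 0.18568.

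| Assumed circumferences (cm) | Σ | V (mL) | Σ at +0.5 cm | Shift | Σ at −0.5 cm | Shift |
|---|---|---|---|---|---|---|
| 16/20/24/25/28/31 | 8,955 | 1,663 | 9,320.25 | +4.1% | 8,597.25 | −4.0% |
| 18/22/26/28/31/33 | 10,810 | 2,007 | 11,211.25 | +3.7% | 10,416.25 | −3.6% |
| 20/24/28/29/32/35 | 12,087 | 2,244 | 12,512.25 | +3.5% | 11,669.25 | −3.5% |

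A 0.5 cm difference at every landmark therefore moves volume by about 3.5–4%. The same error at one landmark only moves it by about 0.3–0.9%.

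**3. What cancels.** Percentage reduction is (VI − VF)/VI × 100. If an examiner's habit multiplies every circumference by k at both visits, both volumes are multiplied by k² and the percentage is unchanged. A constant additive error largely cancels too. Only an error that differs between arms and between baseline and follow-up biases the comparison.

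**4. What a small differential error could do.** The assumptions are no true effect, 45% response in both arms (the protocol's control rate), 30 per group, and an SD of percentage volume change of 5 or 10 points (not in the protocol). The apparent response with a bias of b points is Φ(z₀.₄₅ + b/SD), with z₀.₄₅ = −0.126. Take b = 2, roughly a 0.3 cm difference on the middle arm (2.2%).

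- SD 5: Φ(0.274) = 61%. The chance of a significant result favouring that arm is about 23%.
- SD 10: Φ(0.074) = 53%. The chance is about 9%.

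The nominal value in one direction is 2.5%.

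**5. Sample size.** For 45% versus 80%, two-sided 5% and 80% power, the pooled formula gives 29 per group against the stated 30 (power 81.6% at 30). Blinding the assessor changes none of this.

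**6. What can still be protected.** Trial status reports 115 women included by 24 May 2023: 115/144 = 80%, leaving 29 (20%) to enter. Follow-up runs to 12 months, so later visits remain open for many of those already included.

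**The case against.** **It is disclosed.** The trial calls itself single-blind and says who is blinded. Because {11a} treats therapists and evaluators as one team, the word therapists in Limitations may be meant to include assessors. That is fair: this is an open design choice and not a contradiction. But the reason given applies to delivering treatment, not to reading a bare arm.

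**No extra staff is needed.** A reader might infer this from the role list under {5d}. The documents do not establish it. {11a} pools treatment and evaluation across three people, and no section says physiotherapist 1 delivers no treatment. {19} has the collectors enter the data, and the diaries and cost items (sessions, materials) would reveal the arm. The separation is feasible on paper but has to be written in.

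**A larger error could account for the whole threshold.** A reader might extend the arithmetic to 1.2 cm at all landmarks and claim 10%. Over-reading gives 9.9% on the smallest assumed arm (9,844.2/8,955) but about 8.5% on the largest (13,120.2/12,087). Under-reading, the direction that mimics phase 1 response, gives 9.4% (8,109/8,955) and 8.2% (11,097/12,087). None reaches 10%, and each needs the same error at six points.

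**Baseline is contaminated too.** The documents do not show this. The consent section places the initial evaluation at the consent visit, and no section says the envelope is opened first.

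**Blinding would be imperfect and late.** Both stand. Skin marks, remarks by participants and the twice-weekly bandage visits in group B may reveal the arm, and many day-30 readings are probably already taken. Partial protection of the remaining visits is still worth having.

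**Conclusion.** The concern holds in this form: the protocol leaves the assessor of a manually read primary outcome unblinded, and its stated reason does not cover that assessor. The risk is detection bias that analysis cannot remove. The 3.5–4% shift for 0.5 cm at all six landmarks rests on assumed circumferences, and the false-positive figures also rest on an assumed SD. They show how sensitive the outcome is. They do not show that bias occurred or in which direction, and the actual bias is unknown. The point is a correctable weakness that should be addressed. It does not invalidate the trial, and the remedy now reaches only visits still to come.

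**What to change.** - **Amend {17a}, {17b}, {19} and {5d}** so that the physiotherapist already assigned to reassessments takes no part in randomization, fitting, bandage changes or day-7 contacts, does not handle diaries or cost data, and does not enter or check data that reveal the arm.
- **At each measurement**, have a colleague remove the wrap, bandage or mesh before the assessor enters, ask the participant not to disclose the device, and record the assessor's guess of the arm.
- **Apply this** to all remaining day-30, 6-month and 12-month visits.
- **Settle day 7.** The phase 1 group descriptions list a face-to-face evaluation on day 7, while {18a} lists measurements only before and after the 30 days and at 6 and 12 months. State whether volume is measured on day 7 in phase 1. If it is, a blinded assessor should take it, separately from the treatment contact.
- **In Limitations**, state that assessments already completed were made by unblinded assessors, and give the number.

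The cost is visit scheduling and a stricter division of work in a three-person team whose roles {11a} now pools. Sample size, power and the outcome definition do not change.
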